### Randomization

Baseline characteristics of the subjects will be compiled at informed consent. Subjects will be randomly divided into an intervention arm and a control arm on the day of admission, with the aid of a computer-based randomization module in a 1:1 ratio. Stratified randomization is accomplished using gender, age group (2–4 years, 5–8 years and 9–14 years), residence (rural or urban) and research centre (KCMC or ALMC) as strata. Randomization is performed by the KCMC’s research pharmacist who will then prepare the medication (either the antibiotics or placebo capsules or solution, depending on the age of the child). Both the placebo capsules as well as solution have the same taste and appearance as the amoxicillin capsules and solution. Labelled with only the study protocol number and patients’ details, the medication will be distributed by one of the research nurses. Thus, all health professionals involved in the trial process will be blinded.

### Surgery

All (adeno)tonsillectomies will be carried out under general anaesthesia with the use of orotracheal intubation. Surgery will be performed by all grades of doctors, from residents to specialists. The tonsils are removed using either routine dissection, Sluders technique or electrodissection [7]. Which technique is chosen depends on the surgeon’s experience and preference. Previous studies have shown that the technique does not affect the outcome or the postoperative morbidity [7, 8]. In all patients, the adenoid is removed using a Beckmann adenoid curette.

### Microbial isolates

During surgery, just before dissection of the tonsils, a swab (Copan ESwab; Copan Italia SPA, Brescia, Italy) will be taken from the tonsillar surface for culture and sensitivity. After the operation is completed, one dissected tonsil will be submerged in iodopovidone for around 30 s. Subsequently, the tonsil will be rinsed using sterilized normal saline and divided into two parts with a new sterile blade. Another swab (Copan ESwab; Copan Italia SPA) will be taken from the core of the tonsil.

For patients operated at KCMC, both swabs will be maintained at a temperature between 2 and 8 °C and dispatched within 30 min to the microbiology research laboratory. Samples from ALMC will be stored at a temperature between 2 and 8 °C and transported on the same day to the microbiology research laboratory. At the microbiology research laboratory, all swabs will be incubated at 37 °C for 24 h. After incubation is completed, subcultures from growing microorganisms will be prepared on agar plates. The isolated bacteria will then be Gram stained and microscopically investigated. Only pathogenic organisms will be worked up, no work-ups for normal flora will be done. Microbiological work-up will entirely adhere to the Clinical and Laboratory Standards Institute (CLSI) Performance Standards for Antimicrobial Susceptibility Testing. Antibiotic sensitivity testing will be done for all pathogenic, cultured microorganisms using the disc diffusion test [9]. Discs of the most common antibiotics will be used.

### Postoperative management

After surgery, all patients will be kept in the ward for at least one night. Based on their clinical condition, patients will be discharged. On the ward, patients will receive their labelled medication with either 50 mg/kg amoxicillin or placebo. Medication will be taken 8-hourly for 5 consecutive days. Parents and caretakers are given instructions about the importance of continuing the medication after discharge from the hospital.

All patients will be given paracetamol three times a day and ibuprofen twice a day based on their weight for 10 days. Any additional analgesics or other treatment will be started whenever necessary at the discretion of the treating physician.

### Follow-up

During discharge, a questionnaire will be provided to the persons legally responsible for the participating child. This will be filled out daily and will be presented to the investigator at follow-up visits. The questionnaire is translated, adopted and modified from the standardized Linden et al. [10] post-tonsillectomy follow-up questionnaire (Additional file 1).

On day 7, the wound bed and the general health status will be inspected by the study doctor at the Department of Otolaryngology at KCMC and ALMC respectively. On day 14, a third swab (Copan ESwab; Copan Italia SPA) of the surgical site will be taken and sent to the microbiology research laboratory for culture and sensitivity analysis, as already described. During both visits, detailed information will be obtained by the study doctor. The entire process from patient allocation to follow-up is displayed in Fig. 1 and well described in a SPIRIT (Standard Protocol Items: Recommendations for Interventional Trials) figure in Fig. 2.

**Fig. 1 Fig1:**
[figure not shown]
Flow chart of the trial process from allocation to follow-up. ALMC Arusha Lutheran Medical Centre, KCMC Kilimanjaro Christian Medical Centre

**Fig. 2 Fig2:**
[figure not shown]
Standard Protocol Items: Recommendations for Interventional Trials (SPIRIT) figure of the trial schedule for enrolment, interventions and follow-up/assessments. ALMC Arusha Lutheran Medical Centre, KCMC Kilimanjaro Christian Medical Centre

### Statistical analysis

Continuous variables will be presented as means and standard deviation or median and interquartile range (IQR) if not normally distributed. Categorical data will be presented as a number with percentage. All analysis will be done according to an intention-to-treat protocol.

Differences between the observed risks of events (for primary outcomes of bleeding and fever) between the placebo and antibiotics groups will be calculated along with their 95% confidence intervals. Absolute risks will also be presented as it is important to be aware of the underlying risk of events. Differences in pain score between the two treatment arms will be calculated as mean differences with 95% CIs, using Student’s *t* tests. Secondary outcomes will be analysed using chi-squared tests for categorical data (return to normal activities and microbial recolonization) or Wilcoxon rank-sum tests (days to return to normal diet) for continuous data. *P* < 0.05 will be considered statistically significant. All data will be coded to maximize confidentiality. Collected data will be entered into a database and analysed using IBM SPSS Statistics version 24.

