However, in a Cochrane Review published in 2012, involving 10 trials with a pooled population of 1035 patients, the use of postoperative antibiotics did not show a clinically relevant effect on the haemorrhage rates, the time to resume a normal diet, pain and consequent need for analgesics [5]. Little evidence suggested that prophylactic use of postoperative antibiotics reduced fever. With the existing set of evidence, Dhiwakar et al. advocated against the routine prescription of antibiotics to patients undergoing adenotonsillectomy. However, they did highlight the need for further trials including subgroups of patients who might be in need of selective administration [5]. None of the studies reviewed in this Cochrane Review had been conducted in resource-limited settings. Despite the lack of high-level evidence for postoperative antibiotics, in Tanzania all children receive postoperative antibiotics after adenotonsillectomy based on the assumption that there is a higher risk of postoperative morbidity due to limited resources and a higher burden of infectious diseases. On the other hand, the widespread use of (postoperative) antibiotics is not without risks. There is the individual risk of gastrointestinal and allergic side effects, ranging from vomiting, diarrhoea and rash to severe anaphylaxis. Also, there is the risk of antimicrobial resistance. While global concern for antimicrobial resistances rises, there is still a significant gap of knowledge on this topic in resource-limited settings, like Tanzania. In developing countries, amoxicillin is one of the most misused and wrongly prescribed drugs. The majority of young children suffering from acute respiratory infection symptoms are treated inappropriately with this antibiotic. Cross-sectional research from 2018, performed in Moshi, Tanzania, found that 92.3% of retailers dispensed antibiotics without prescriptions [6]. This practice disadvantages most inhabitants of these areas in particular. Cross-resistance and cost in obtaining superior antimicrobial agents become a big challenge.

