### Study objective

The study objective is to compare the postoperative morbidity following elective (adeno)tonsillectomy in children treated with postoperative amoxicillin or a placebo in northern Tanzania. We hypothesize that placebo is non-inferior to amoxicillin in preventing postoperative morbidities following (adeno)tonsillectomy in children in northern Tanzania.

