### Study sample

Postoperative bleeding, fever and pain were used as primary outcomes. We calculated power for all primary outcomes and only took the outcome with the largest number of participants. Based on the latest Cochrane Review, titled “Antibiotics to reduce post-tonsillectomy morbidity” [5], 2.5% of all patients who undergo an elective tonsillectomy have a significant postoperative haemorrhage. With this haemorrhage rate, a significance level (α) of 0.05, a power (π) of 0.80 and a non-inferiority margin of 5%, we calculated the number of patients in our intervention group. The group treated with antibiotics should include 121 patients, giving a total of 242 patients necessary for analysis. To allow for some loss to follow-up, the aim is to include 270 children.

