### Study limitations

Children coming from distant areas surrounding the hospital might not return for follow-ups and therefore the loss to follow-up rate might be higher than estimated. This in turn could result in inadequate sample sizes. We will try to reduce the amount of subjects lost to follow-up by implementing reimbursement of travel expenses.

Different surgical techniques will be used in performing (adeno)tonsillectomy. This can be routine dissection, Sluder technique or electrodissection, according to the preference and custom of the surgeon performing the operation. As a consequence of this, the use of coagulation may differ within subjects. This, in turn, could result in differences in prevalence of pain and infection postoperatively. Still, up to now there are insufficient data to prove that one method of tonsillectomy is superior to the others [8].

In Tanzania, it is a custom that relatives oversee patients’ medication supply and intake. Although all patients are prescribed the same amount of analgesics, it is not regular practice that nurses supervise the medication intake. This could influence the patients’ perception of pain. Moreover, flushing of the wound bed with water postoperatively might decrease the infection risk following (adeno)tonsillectomy. This, however, is a management factor which is difficult to standardize and could therefore influence the outcomes.

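### All analyses are fixed as intention-to-treat in a non-inferiority trial, with no supporting adherence-based analysis to show whether dilution has produced the result

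*Protocol article*

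**What the plan says.** All references are to the protocol article.

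- **Study objective:** "We hypothesize that placebo is non-inferior to amoxicillin in preventing postoperative morbidities".
- **Study sample:** the calculation uses a significance level of 0.05, power of 0.80 and a 5% non-inferiority margin, applied to a 2.5% haemorrhage rate. The result is given as: "The group treated with antibiotics should include 121 patients, giving a total of 242 patients necessary for analysis". The enrolment target is 270.
- **Statistical analysis:** "All analysis will be done according to an intention-to-treat protocol". Bleeding and fever are compared by risk differences with 95% confidence intervals. No per-protocol, as-treated or adherence-adjusted analysis is named.
- **Postoperative management:** study medication is given every 8 hours for 5 days, and children may go home after one night. Carers are told why the course should be continued. The section adds: "Any additional analgesics or other treatment will be started whenever necessary at the discretion of the treating physician".
- **Study limitations:** relatives customarily look after medication supply and intake, and "it is not regular practice that nurses supervise the medication intake".
- **Background:** a 2018 study in Moshi, where one of the two centres is, "found that 92.3% of retailers dispensed antibiotics without prescriptions".
- **Study population:** the exclusion for antibiotic use covers the time of surgery and the week before it, not the period afterwards.

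**The concern.** In a superiority trial, non-adherence and crossover work against the claim, so intention-to-treat alone is the cautious choice. In a non-inferiority trial the same mixing works for the claim: the observed difference shrinks and falls more easily inside the margin. Intention-to-treat is not an error here, but on its own it cannot show whether a favourable result reflects equivalent outcomes or similar antibiotic exposure in the two arms.

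The word *all* makes this a stated choice rather than a detail left open. An analysis plan that added a per-protocol set would depart from the article. The trial is meant to change prescribing in Tanzania and elsewhere, so a falsely reassuring result would have consequences beyond the two centres.

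**Working it through.** **Step 1. Reproduce the planned sample size.** Inputs from Study sample: 2.5% in both arms, margin 0.05, power 0.80.

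n per arm = (z₁₋α + z₀.₈₀)² × 2 × 0.025 × 0.975 / 0.05²

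- One-sided α = 0.05: (1.645 + 0.842)² × 0.04875 / 0.0025 = 120.6, so 121 per arm and 242 in total. This matches the article exactly.
- One-sided α = 0.025: 153.1, so 154 per arm and 308 in total. This does not match.

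The calculation therefore corresponds to one-sided 5%, while the analysis reports 95% confidence intervals (one-sided 2.5%). Both are shown below.

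**Step 2. Dilution model.** Suppose that under full adherence the true difference equals the margin: 7.5% on placebo against 2.5% on amoxicillin. Let x be the share of the amoxicillin arm that is effectively untreated, and y the share of the placebo arm taking effective outside antibiotics. Both are assumptions; the article gives neither.

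- Amoxicillin risk = 0.025 + 0.05x
- Placebo risk = 0.075 − 0.05y
- Observed difference = 0.05 × (1 − x − y)

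**Step 3. Chance of declaring non-inferiority, 121 per arm.**

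P = Φ[(0.05 − difference)/SE − z₁₋α], with SE = √{[p₁(1 − p₁) + p₂(1 − p₂)]/121}

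Example with x = 20%, y = 10%: risks 0.035 and 0.070, difference 0.035, SE = √[(0.0338 + 0.0651)/121] = 0.0286. Then 0.015/0.0286 = 0.525, and Φ(0.525 − 1.645) = Φ(−1.120) = 0.131. On a 95% interval, Φ(0.525 − 1.960) = 0.076.

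| x (amoxicillin untreated) | y (placebo with outside antibiotic) | Observed difference | One-sided 5% | 95% CI |
|---|---|---|---|---|
| 0% | 0% | 5.0 points | 5.0% | 2.5% |
| 10% | 0% | 4.5 points | 7.1% | 3.7% |
| 10% | 10% | 4.0 points | 9.9% | 5.5% |
| 20% | 10% | 3.5 points | 13.1% | 7.6% |
| 20% | 20% | 3.0 points | 17.6% | 10.7% |

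Binomial simulation of the same rule (400,000 runs) gives somewhat higher values throughout: 7.2% and 3.5% with no mixing, 16.1% and 9.0% at 20%/10%. The pattern is the same.

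**Step 4. A careless per-protocol set can lean the same way.** Suppose 10% of placebo children are given antibiotics because of early symptoms, and these children would have had a 25% risk untreated (assumed). Dropping them leaves a placebo risk of (0.075 − 0.10 × 0.25)/0.90 = 5.6%, so the difference becomes 3.1 points. With about 109 placebo and 121 amoxicillin children, SE = 0.0261 and P = Φ(0.0194/0.0261 − 1.645) = about 18% at one-sided 5%. That is no better than the 13% at 20%/10% in Step 3.

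**Step 5. Precision of an adherent set.** If 20% of each arm is incomplete and 10% of placebo children take outside antibiotics, 121 × 0.8 × 0.9 = 87 placebo and 121 × 0.8 = 97 amoxicillin children remain. With 2.5% in both arms, SE = √[0.024375 × (1/87 + 1/97)] = 0.0231. Power is Φ(0.05/0.0231 − 1.645) = about 70%, against 80% with 121 per arm. On a 95% interval it is about 58% against 70%.

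**The case against.** Several points on the other side stand.

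- **Non-adherence is not documented.** A reader might infer that missed doses and crossover are expected. The article does not say so. The remark about nurse supervision sits in a sentence on analgesics, and the consequence drawn is for pain perception; only the preceding remark about relatives overseeing medication is general. The 92.3% is a share of retailers, not of trial children taking antibiotics. The discretion clause does not mention antibiotics. Matched placebo, blinded staff and instructions to carers all work against mixing. What the text supports is plausibility.
- **The bias is conditional.** If amoxicillin has no effect, mixing does not distort the comparison. The Background reports that a pooled review of 10 trials and 1035 patients found no clinically relevant effect on haemorrhage. Still, a non-inferiority test exists to guard against the case where the effect is real.
- **The illustration is demanding.** It lets haemorrhage triple without amoxicillin and treats mixing as all-or-nothing. Partial adherence would dilute less.
- **Intention-to-treat answers the policy question.** Real-world adherence and outside antibiotics are part of what happens when routine prescribing stops. This is a good reason to keep it primary, but not to exclude every other analysis.
- **The sentence may name only the primary principle**, with supporting sets left to an analysis plan that is not shown. The word *all* makes that reading hard to sustain.

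A reader might also infer that both analyses should have to meet the margin. Steps 4 and 5 argue against such a gate: the second analysis can share the bias, and the joint requirement costs power.

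**Conclusion.** The concern holds in a limited form. The article commits every analysis to intention-to-treat while testing non-inferiority, and so leaves no check on dilution. If amoxicillin truly reduces haemorrhage, modest mixing raises the false non-inferiority rate: roughly doubled when 10% of each arm is mixed, and more than tripled at 20% of each arm. These figures rest on a true difference at the margin, 121 per arm, the normal approximation and assumed mixing rates. They show direction and possible size; they are not estimates for this trial.

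The documents do not support saying that intention-to-treat is wrong, that the result will be biased, or that the sample size is in error on this ground. Nor can it be said that adherence goes unrecorded: the daily questionnaire is an additional file that is not shown, and the study doctor collects detailed information at both visits.

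**What to change.** Amend the Statistical analysis section as follows.

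1. Keep intention-to-treat as the primary analysis, and add a prespecified supportive per-protocol or adherence-adjusted analysis of the primary outcomes. Apply the non-inferiority margin to haemorrhage, the only outcome for which the article states one.
2. Define the adherence set by study doses taken and by non-study antibiotics that were not prompted by a suspected outcome. Children given antibiotics for early fever, pain or bleeding stay in the set, or are counted as events in a sensitivity analysis.
3. State that a non-inferiority conclusion will be interpreted cautiously if the two analyses disagree.
4. Make sure that doses taken and non-study antibiotics, with the reason for starting them, are recorded in the daily questionnaire or at the day 7 and day 14 visits, if they are not already.

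The cost is a little more data collection, one further analysis, and a smaller set with wider intervals. Keeping 121 per arm in that set would need 2 × 135 = 270 enrolled with 10% excluded for any reason, 2 × 152 = 304 with 20%, and 2 × 173 = 346 with 30%. The planned 270 covers total exclusions of 1 − 242/270 = 10.4%, loss to follow-up included. The analysis should therefore be supportive and not co-primary, and on that footing no change to the sample size is needed.

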### Primary outcomes

The primary outcome is post-(adeno)tonsillectomy morbidity, but morbidity cannot be measured as a single parameter. Postoperative haemorrhage and infection are the most important postoperative complications contributing to post-(adeno)tonsillectomy morbidity. Post-(adeno)tonsillectomy infection is difficult to define since the tonsillar beds are left to heal by secondary intention after surgery in a bacterial, mucosal environment. Typical symptoms of surgical site infection are therefore absent. Clinically worsening pain and raised temperature are thus considered features of infection. For this reason, postoperative haemorrhage, raised temperature (fever) and pain are the primary outcomes in this research.

Postoperative haemorrhage is defined using two parameters: major if warranting re-admission, blood transfusion or return to theatre for haemostasis; and minor if any recorded postoperative blood loss (i.e. spitting of blood saliva 24 h post operation). Fever is defined as temperature greater than 38 °C on 2 consecutive postoperative days or greater than 39 °C on any postoperative day, and postoperative pain is rated using the Wong-Baker FACES® Pain Rating Score.

Temperature will be taken daily by the research nurse while admitted and thereafter by the parent/caretaker with an axillary thermometer until the 7th postoperative day.

The Wong-Baker FACES® Pain Rating Scale will be used to assess children’s pain perception postoperatively. Written permission has been granted from Wong-Baker FACES Foundation for using both the English (while in hospital) and Swahili (while at home) Wong-Baker FACES® Pain Rating Scale in this study. The consequent need for analgesics will be documented by the prescribing physician.

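### Pain, a primary outcome rated repeatedly, is compared by an unadjusted t test on one undefined pain score, which does not address the worsening that justified the outcome

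*Protocol article*

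**What the plan says.** The Primary outcomes section states that "postoperative haemorrhage, raised temperature (fever) and pain are the primary outcomes in this research". Its reason for including pain is that "Clinically worsening pain and raised temperature are thus considered features of infection". The outcome itself is given only as "postoperative pain is rated using the Wong-Baker FACES® Pain Rating Score", with no assessment day and no summary attached.

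Each child is rated more than once: the same section describes "using both the English (while in hospital) and Swahili (while at home") versions of the scale. On the take-home questionnaire, the Follow-up section says "This will be filled out daily and will be presented to the investigator at follow-up visits".

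The Statistical analysis section then fixes the comparison: "Differences in pain score between the two treatment arms will be calculated as mean differences with 95% CIs", by Student's t tests. No covariates are mentioned. The Randomization section stratifies by gender, age group, residence and centre.

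**The concern.** A two-sample t test takes one value per child. The article describes several ratings per child and does not say which value, or which combination of values, enters the test. Fever shows the contrast: its repeated temperatures are reduced to one event per child by an explicit rule in the Primary outcomes section. Pain has no such rule.

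Three things follow for a primary outcome.

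- The day or summary can be chosen after the data are seen, so the result can depend on that choice.
- The repeated scores and the stratification factors have no stated role. The Study strengths section itself names young age as a likely contributor to worse outcomes, so at least one stratification factor is thought to be prognostic.
- A difference in mean level is not a measure of worsening. The Study objective is to show placebo non-inferior, so a late excess of pain on placebo that is diluted or missed would favour that conclusion.

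**Working it through.** **Inputs from the article.** Analysis: mean difference with 95% CI by Student's t tests, significance at P < 0.05. Sample size: 121 per arm, 242 in total (Study sample). No standard deviation, difference or margin for pain is given, so no sample size for pain can be recomputed.

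**Assumptions of this check.** Seven daily scores per child, equal variance on each day, the same within-child correlation ρ between any two days with ρ from 0.3 to 0.7, and a two-sided 5% test. The article gives neither the number of pain scores nor ρ.

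**The plan's own figure.** With 2.5% haemorrhage in both arms, a margin of 5 percentage points, 80% power and one-sided α = 0.05: 2 × 0.025 × 0.975 × (1.645 + 0.842)² / 0.05² = 120.6, so 121 per arm. This reproduces the stated number. It concerns haemorrhage and is used below only as the number of children per arm.

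**One day against all days.** Relative to a single day, the variance of a 7-day per-child mean is (1 + 6ρ)/7, and the standard error ratio is its square root. For a single day, the difference detectable with 80% power is (1.96 + 0.84) × √(2/121) = 0.36 SD. For the mean, this is multiplied by the ratio.

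| ρ | Variance ratio | SE ratio | Cut in SE | Detectable difference, 7-day mean (single-day SD) |
|---|---|---|---|---|
| 0.3 | 2.8/7 = 0.400 | 0.632 | 37% | 0.23 |
| 0.5 | 4.0/7 = 0.571 | 0.756 | 24% | 0.27 |
| 0.7 | 5.2/7 = 0.743 | 0.862 | 14% | 0.31 |

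**A separate test on each day.** Simulating 200,000 sets of seven equally correlated normal test statistics, the chance that at least one exceeds 1.96 in absolute value with no true difference is 27%, 23% and 18% for ρ = 0.3, 0.5 and 0.7.

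**A late rise.** Suppose placebo is 1 point worse on days 5 to 7 only. A day-1 comparison shows 0. A 7-day mean shows 3/7 = 0.43 points. A contrast of days 5–7 with days 1–3 shows the full 1 point. The size and timing of this rise are illustrative.

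**Is the t test itself invalid?** No. In 4,000 simulated trials with 121 children per arm and seven days at each ρ, a t test on the per-child mean or on the per-child slope kept its error at about 5%. The fault lies in the undefined variable and in what the comparison leaves out.

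**The case against.** The strongest reply is that the article condenses a full protocol, that a statistical analysis plan may exist, and that the schedule figure and the questionnaire (Additional file 1) are not shown. Any of these may define the pain variable. This stands as a limit on the point. It does not remove it, because the article does more than stay silent: it commits a primary outcome to a named, unadjusted test while describing data that the test cannot take without a further definition.

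A second reply is that worsening pain is only the rationale, and that the outcome as defined is a rating, so comparing levels is no contradiction. That is fair as far as it goes. Still, an analysis of level alone leaves the stated reason for the outcome unexamined, and this can be seen from the text without any hidden file.

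Third, a mixed model is partly a preference. With complete data its average arm difference is close to a t test on per-child means, apart from the adjustment. That is correct, and it is why an adjusted per-child summary is acceptable. The average alone would also dilute a late rise, so a separate contrast is needed under either approach.

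A reader might go further and infer any of the following. The article does not support them.

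- *The t test must either discard days or treat days as independent.* A per-child mean, peak, change or slope does neither.
- *The true error rate is 24% to 39%.* That is what pooling 7 days as independent would give for ρ of 0.3 to 0.7, but the article nowhere says that child-days will be pooled.
- *A t test cannot show worsening.* A t test on slope or change could; none is planned in the text.
- *Daily pain scores on days 1 to 7 are stated.* The explicit daily schedule, "Temperature will be taken daily by the research nurse while admitted and thereafter by the parent/caretaker" until day 7, is for temperature. For pain, daily scoring is inferred from the daily questionnaire.

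**Conclusion.** The point holds in a limited form. The protocol article compares a repeatedly rated primary outcome by an unadjusted t test on a pain score that it does not define. This leaves the day or summary open, gives the repeated scores and stratification factors no role, and does not examine worsening.

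The size depends on what would be done. If one day were used, the standard error would be larger than necessary: using all days would cut it by 37% to 14%. If each day were tested, the chance of at least one false positive would be about 18% to 27%. Both ranges rest on the assumed seven scores and equal correlation of 0.3 to 0.7. The gain from adjusting for the stratification factors cannot be quantified from the article. The mismatch between worsening as rationale and mean level as analysis rests on the text alone. This is a weakness that should be corrected, not a demonstrated error in the test.

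**What to change.** Before unblinding, replace the t test with a repeated-measures linear mixed model on the recorded Wong-Baker scores, with arm, day, arm-by-day and the randomisation factors (gender, age group, residence, centre), and child as the repeated unit. Name the days from the questionnaire as actually used. Take the average arm difference over those days, with its 95% CI, as the primary pain estimate. Prespecify a late-versus-early arm-by-day contrast, with its days named, to address worsening.

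An acceptable alternative is a prespecified per-child mean plus a per-child change, each compared between arms with adjustment for the randomisation factors.

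The change is to the analysis wording and uses scores the trial already plans to collect. SPSS, the named software, fits the model. The model can also use partly completed diaries, which helps because the Study limitations section expects some children from distant areas not to return. The downside is slightly more analysis work.

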Summarizing the aforementioned, the widespread use of postoperative antibiotics after (adeno)tonsillectomy in children in Tanzania may have more negative effects than benefits, if there are any benefits at all. To limit unnecessary antibiotic prescription and secondary antibiotic resistance, well-designed randomized controlled trials are needed. This randomized double-blind placebo-controlled trial studies the prophylactic effect of antibiotics on morbidity after adenotonsillectomy in children in Tanzania.

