### Secondary outcomes

The secondary outcomes include the time until normal diet is resumed, time until normal activities are resumed and occurrence of adverse events (rash, vomiting, diarrhoea and anaphylaxis) and microbial recolonization of the tonsillar niche.

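### The stated analysis gives adverse events counts, percentages and at most a chi-squared test, while risk differences with 95% CIs are stated only for bleeding and fever

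*Protocol article*

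**What the plan says.** All references are to the protocol article.

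- **Secondary outcomes** includes "occurrence of adverse events (rash, vomiting, diarrhoea and anaphylaxis").
- **Background** names gastrointestinal and allergic side effects as individual risks of antibiotics. It concludes that widespread postoperative use "may have more negative effects than benefits, if there are any benefits at all".
- **Statistical analysis**, on the primary binary outcomes: "Differences between the observed risks of events (for primary outcomes of bleeding and fever) between the placebo and antibiotics groups will be calculated", with 95% confidence intervals.
- **Statistical analysis**, on the secondary outcomes: "Secondary outcomes will be analysed using chi-squared tests for categorical data (return to normal activities and microbial recolonization) or Wilcoxon rank-sum tests", the latter for days to normal diet. The threshold is P "< 0.05 will be considered statistically significant".
- **Statistical analysis**, on description: "Categorical data will be presented as a number with percentage".

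Adverse events are not mentioned by name in the Statistical analysis section, and the article gives no expected adverse-event rate.

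**The concern.** The hypothesis is that placebo is non-inferior to amoxicillin on postoperative morbidity. If that is shown, the practical argument for dropping the antibiotic is that children avoid its side effects, so readers will want to set avoided harm against any lost benefit. The article estimates the benefit side (bleeding, fever) as a risk difference with an interval. For the harm side it fixes a significance test and no estimate of the difference.

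The sample size was set for haemorrhage non-inferiority, not for adverse events. For uncommon events, a non-significant test in a trial of this size says little about whether a worthwhile excess exists. An interval would show directly how large an excess remains compatible with the data.

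**Working it through.** **Inputs from the article.** Study sample: 121 analysed per arm (242 in total, 270 enrolled), haemorrhage rate 2.5%, margin 5 points, α 0.05, power 0.80. Statistical analysis: chi-squared test, P < 0.05, taken here as two-sided.

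**Inputs assumed.** Adverse-event rates. The article gives none, so a range is shown.

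**Step 1. Reproduce the plan's own sample size.** With equal rates in both arms, n = (z_α + z_β)² × 2p(1 − p) / margin².

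- One-sided α 0.05: (1.645 + 0.842)² × 2 × 0.025 × 0.975 / 0.05² = 6.18 × 19.5 = 120.6, so 121 per arm. This matches.
- One-sided α 0.025 would give 154.

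The figure of 121 is therefore sized on haemorrhage, at one-sided 5%.

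**Step 2. Power of the chi-squared test for a doubled rate, by formula.** Power = Φ[(d − 1.96 × SE₀) / SE₁], with SE₀ from the pooled rate and SE₁ from the separate rates. For 5% v 10%:

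- SE₀ = √(2 × 0.075 × 0.925 / 121) = 0.03386
- SE₁ = √((0.05 × 0.95 + 0.10 × 0.90) / 121) = 0.03371
- Power = Φ[(0.05 − 1.96 × 0.03386) / 0.03371] = Φ(−0.486) = 0.31

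**Step 3. The same by exact enumeration** over all pairs of binomial counts, 121 per arm:

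| Assumed rates | Uncorrected chi-squared | With Yates correction |
|---|---|---|
| 1% v 2% | 7% | 1% |
| 2.5% v 5% | 16% | 9% |
| 5% v 10% | 31% | 23% |
| 7.5% v 15% | 46% | 38% |
| 10% v 20% | 60% | 52% |
| 15% v 30% | 81% | 76% |
| 20% v 40% | 93% | 91% |

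Uncorrected power for a doubling passes 50% at a lower-arm rate of about 8.3% (8.4% by the formula) and reaches 80% at about 15%. If all 135 per arm were analysed, these thresholds by the formula fall to about 7.6% and 13.8%.

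**Step 4. What an interval would add.** Take 12/121 on amoxicillin and 6/121 on placebo.

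- Chi-squared = 242 × (12 × 115 − 6 × 109)² / (121 × 121 × 18 × 224) = 2.16, P = 0.14.
- Risk difference = 9.9% − 5.0% = 5.0 points.
- Wilson limits are 5.8% to 16.5% and 2.3% to 10.4%. The Newcombe 95% CI combines them:
  - lower: 0.0496 − √((0.0992 − 0.0576)² + (0.1040 − 0.0496)²) = −0.019
  - upper: 0.0496 + √((0.1654 − 0.0992)² + (0.0496 − 0.0229)²) = 0.121

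The test alone says not significant. The interval, −1.9 to 12.1 points, says that an excess of up to about 12 points is not excluded.

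**The case against.** **The article does cover adverse events.** The general rule sends categorical secondary outcomes to chi-squared tests, and the outcomes in the parenthesis can be read as examples. Tabulation details commonly sit in the full protocol or SAP, neither of which is shown. This stands: the absence of adverse events from the parenthesis is not itself a finding. The point is the method the rule fixes, a test without an estimate, when the same section states a better method for two other binary outcomes.

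**Counts and percentages will be shown.** This also stands. A reader could derive the difference and its interval, so the comparison does not rest on the P value alone. It is still left to the reader for harms and done by the trial for bleeding and fever.

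**A reader might infer that any doubling of harm would usually be missed.** The documents do not support this. They give no adverse-event rate, and for commoner events a doubling would usually be found (about 60% power at 10% v 20%, 93% at 20% v 40%).

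**A reader might infer that a non-significant result will be reported as no difference in harm.** The article says only which P values count as significant. It does not say how a non-significant result will be worded.

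**A reader might infer that the chi-squared test is invalid for sparse counts.** This is weak. Exact enumeration at 121 per arm keeps the type I error of the uncorrected test below 5% at common rates of 0.5% to 3%.

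**Weighing harm against benefit is background, not the stated objective, and an interval adds no power.** Both are correct. The objective is postoperative morbidity, and an interval for an uncommon event will often be inconclusive. It does show how inconclusive, which the test does not. Six-monthly safety monitoring is provided, but that does not replace a between-arm estimate in the final report.

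**Conclusion.** The concern holds in a limited form. For a declared secondary outcome that forms part of the trial's rationale, the article's stated method yields counts, percentages and at most a chi-squared test at P < 0.05, whereas bleeding and fever get risk differences with 95% CIs.

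The consequence is conditional on the event rate. With 121 per arm and an assumed lower-arm rate below about 8%, a doubling would be non-significant more often than not. Above that rate it would more often be detected, and power reaches about 80% at a lower-arm rate of 15%. These figures assume an uncorrected two-sided test; the Yates correction moves the 50% point to just under 10%.

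This does not affect the primary analysis or the sample size. It is worth changing because the better method is already used in the same section and costs almost nothing.

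**What to change.** In Statistical analysis, extend the risk difference with 95% CI to adverse events:

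- Name each of rash, vomiting, diarrhoea and anaphylaxis, and add any adverse event.
- For each, give the number and percentage of children per arm and the risk difference, amoxicillin minus placebo, with a 95% score (Newcombe) interval.
- Present these beside the bleeding and fever differences, with the direction of subtraction labelled.
- State that a non-significant P value will not be read as absence of harm.

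**Cost.** One or two sentences, using data already being collected, with no extra children, visits or change in treatment. The small downside is that the intervals will be wide for uncommon events and will show that moderate excesses cannot be excluded.
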